***Intervention or treatment:***

The intervention that will be tested will be a short “soap opera” style waiting room video with three interwoven vignettes that incorporate key prevention messages aimed at increasing early treatment initiation, treatment adherence, retention in care, and partner protection for people with HIV. The video will contain characters who represent various populations, including women, gay men, heterosexuals, African-Americans, and Latinos. The video will also include a short animation focusing on treatment adherence. The video is meant to play in the waiting room throughout the day for 10 months. Optimally, the video will play on a continuous loop. Some facilities may need short pauses between video replays based on their local circumstances. If this need arises, the pause interval will be discussed with and approved by CDC.

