**Appendix 2: Observation Protocol**

**Waiting Room Observation Protocol**

Scheduling: Systematic observations will be conducted within the first 3 months of the beta-test period to increase the likelihood that the patients being observed are seeing the video for the first time.

Checking in: At the beginning of the shift, observer will check in with the clinic manager, determine which video playback option is being used (i.e., continuous play, 10-minute interval between cycles, 20-minute interval), determine which waiting room seats do **not** offer a clear (unobstructed) view of a video monitor, and find a seat to begin the observation.

Finding a spot for the observation: Observer will find an open seat where he/she will be able to watch patients’ reactions from the most unobtrusive location possible. The patients should not be behind the observer. The observer may change positions if his/her position is not working well.

All data will be entered on a tablet using a Survey Monkey data collection instrument. Each assessment will have four sections:

1. **Initial waiting room conditions**
2. **Systematic observation of all waiting room patients during one video cycle**
3. **Systematic observation of select waiting room patients during the next video cycle**
4. **Summary comments**

The observer will complete one assessment for every two cycles of the video. The observer will continue to complete the assessments until he/she has completed an 8-hour shift (6-8 assessments).

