**2. Systematic observation of waiting room patients**

Observer will begin this observation at the beginning of the video (i.e. video Opening shots and title) and will continue this observation through each segment of stories or animation in the video for one full cycle of the video. The observer will concentrate on patients who were not present during the previous video cycle. The observer will look around the room going from patient to patient, covering all patients that can be seen from his/her vantage point, to observe their reactions. The main objective of this section is to note any points in the video that seemed to hold patients’ attention, not hold attention, or elicit a positive or negative reaction such as laughter, discussion, or disengagement with the video. Patients who are multi-tasking while watching the video will be considered to be watching the video. Observer will use the time during the credits to note additional general observations for this cycle.

The variables collected in this section include:

- Number of patients by apparent age
- Number of patients by apparent race/ethnicity
- Number of patients by apparent gender
- Number of patients who have a clear view of a video monitor
- Number of patients in the waiting room that the observer can see (to measure engagement with video)
- Number of patients in the waiting room who were present for the previous cycle.
- General observations about engagement with all video segments for all patients for this cycle

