**3. Systematic observation of select waiting room patients**

Observer will randomly choose four patients who have a clear view of the video, attempting to get a diverse sample regarding age, gender, and race/ethnicity. Patients who were not present in the previous cycle should be chosen, unless there are fewer than four patients in the waiting room who were not present during the previous cycle. If one or more of the four patients was present for the previous cycle, note this on the Survey Monkey instrument.

The observer will watch these four patients for one video cycle. Observer will begin this observation at the beginning of the video (i.e., Opening) and will continue this observation through each segment of stories or animation in the video for one full cycle of the video. The observer will record all reactions and behaviors that occur during each segment. For example, a patient may begin watching the video, have a negative reaction, and stop watching the video during a segment. If a patient is absent during one or more segments of the video during the cycle, the observer will check the “N/P” box for that patient’s reactions for those segments (e.g., if the patient leaves in the middle of a story, the observer will mark what occurred for that patient up until the time he or she leaves, and enter N/P for the rest of his or her segments). If there are fewer than 4 people in the waiting room to observe initially, the observer will enter N/P for the missing patients’ segments. However, if one or more patients subsequently enter the waiting room during this cycle, the observer should begin recording these patients.

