### 2f. How many of these patients were present for any portion of the previous video cycle?

|  |
| --- |

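### With a continuous loop and presence read as any portion of the previous cycle, essentially no patient seated at the Opening meets the new-viewer preference, and the Yes/No flag cannot grade prior exposure

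*Protocol*

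**What the plan says.** **Playback.** Section III.C (Intervention or treatment) gives the preference: "Optimally, the video will play on a continuous loop". Short pauses are allowed where a site needs them. Appendix 2 has the observer find out at check-in which option is running: "continuous play, 10-minute interval between cycles, 20-minute interval".

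**Whole-room half.** Appendix 2, part 2, covers every patient the observer can see, with an emphasis: "The observer will concentrate on patients who were not present during the previous video cycle".

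**Select-patient half.** Appendix 2, part 3, uses the next cycle and begins at its first moment: "Observer will begin this observation at the beginning of the video (i.e., Opening"). Four patients are chosen at random with an eye to demographic diversity. The preference is: "Patients who were not present in the previous cycle should be chosen, unless there are fewer than four patients in the waiting room". The condition in full reads: "unless there are fewer than four patients in the waiting room who were not present during the previous cycle". When the fallback is used: "If one or more of the four patients was present for the previous cycle, note this on the Survey Monkey instrument".

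**The form.** Item 3a in Appendix 3 has a Yes/No column for presence at the previous cycle, for four patients and four replacements. It does not say how much presence counts. Item 2f, the whole-room count, does: "How many of these patients were present for any portion of the previous video cycle".

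**The purpose.** The bias discussion in Section III.D and the scheduling note in Appendix 2 both place the observation days early so that earlier exposure to the video distorts reactions less. Section III.A says that less engaging segments will be reworked.

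**The concern.** The preference and the flag exist to keep previous exposure out of the engagement data. Under the playback that the protocol prefers, and under the only definition of presence that it gives, neither does so. The preference is not met, and the flag takes one value.

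The data at stake are those used to decide which segments to change. The analysis plan in Section III.D takes duration of engagement by segment, and the search for scenes that lose attention, from the select-patient half. A patient who looks away from a segment that played shortly before, on the same visit, may simply have seen it. Without a record of what had already played, that is indistinguishable from a weak segment. The effect is also uneven: it falls more on later segments than on the Opening.

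**Working it through.** The protocol has no figure of its own to reproduce. The main step is logical. The later figures are illustrations, because neither video length nor waiting time is stated.

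**1. Who qualifies at the Opening.** On the item 2f reading, a qualifying patient must arrive after one cycle ends and before the next begins.

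- Expected number qualifying = arrival rate × gap.
- Continuous play: gap = 0, so expected number = rate × 0 = 0 at any arrival rate.

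The fallback therefore applies at essentially every select-patient assessment, and all four starting patients are marked Yes. The first cycle of the day is no exception for this half, because the select-patient cycle always follows a whole-room cycle.

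**2. What the Yes conceals.** Segment order is taken from the form: Opening, Story 1, Animation 1, Story 2, Animation 2, Story 3, then credits.

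| Arrived in previous cycle during | Flag (item 2f reading) | New on this visit | Already played, wholly or partly |
|---|---|---|---|
| Opening, or earlier | Yes | none | all six |
| Animation 1 | Yes | Opening, Story 1 | Animation 1, Story 2, Animation 2, Story 3 |
| Story 3 | Yes | first five | Story 3 |
| Credits | Yes | all six | none |

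Story 3 has already played, at least in part, for everyone except those who arrived during the credits. The Opening has already played only for those present since the previous Opening or earlier.

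**3. How many are partial viewers (illustration).** Under continuous play, let L be video length and w the mean wait. The share of those seated at the Opening who arrived after the previous Opening began is 1 − exp(−L/w) for exponential waits, or min(1, L/w) for fixed waits.

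- L = 30 min, w = 20 min, exponential: 1 − exp(−1.5) = 78%.
- L = 30 min, w = 60 min, exponential: 1 − exp(−0.5) = 39%.
- L from 15 to 40 min and w from 20 to 60 min, both wait models: 22% to 100%.

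**4. Sites with a pause (illustration).** The protocol expects 192 to 336 patients observed over three sites, or 64 to 112 per site. Taking these as arrivals over 480 minutes gives 0.133 to 0.233 per minute. It is further assumed that all who arrive in the pause are still there, with a clear view, at the Opening. The number qualifying is taken as Poisson.

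| Pause | Expected qualifying | P(at least 4) |
|---|---|---|
| 10 min | 1.3 to 2.3 | 5% to 21% |
| 20 min | 2.7 to 4.7 | 28% to 69% |

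Under these assumptions the fallback would be frequent at paused sites too.

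**5. Playback on the form.** The initial-conditions list in Appendix 2 and items 1a to 1e have no field for the playback option that the observer establishes at check-in.

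**The case against.** The strongest objection is that the zero depends on a definition borrowed from another item. The words *any portion* stand only in item 2f. Part 3 of Appendix 2 and item 3a leave presence undefined, and if it means the whole cycle, mid-cycle arrivals qualify and the preference works. This stands as a limit on the claim. It does not clear the form: the two items would then use different meanings of presence, and a No would still cover both a patient who arrived late in the Opening and one who arrived during the credits.

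A reader might infer that the observation rests on repeat viewers. The documents do not support that. A Yes means presence for some of the previous cycle, and many such patients are new to the early segments. Nor does the rule leave the observer with nobody to watch, because the fallback lets observation proceed.

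A reader might also infer that both halves are confined to new viewers. The whole-room half only emphasises them. In the select-patient half, late arrivals are recorded when fewer than four people are present at the start, and some replacements may be new. These routes are narrow, since the observer is asked to identify replacements at the start of the cycle where possible.

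Finally, a reader might infer that differences between facilities are confounded with playback. That requires the sites to differ in playback, and the protocol does not say that they do. It is also fair that Hypothesis 1 does not itself require first viewings, and that this is a developmental, largely qualitative exercise with stated limits.

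**Conclusion.** The point holds in a limited form. Given continuous play and the item 2f meaning of presence, essentially no patient seated at the Opening meets the preference, and the item 3a flag carries no information about the four starting patients. On the other reading, items 2f and 3a conflict and the flag is still too coarse. Either way, the form cannot show which segments a select patient had already been exposed to on that visit, although limiting bias from previous exposure is the protocol's own aim.

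The size of any distortion in segment engagement cannot be computed from the document. Its direction follows from segment order: prior exposure is greatest for Story 3 and least for the Opening. The shares for partial viewers and paused sites rest on assumed waits, video length and arrivals, and should not be quoted as properties of the study. No stated sample size or test of the medical-record outcomes is affected. This is a worthwhile, inexpensive correction to the select-patient half, not a fault that invalidates the observation.

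**What to change.** 1. **Item 3a.** For the four select patients and their replacements only, replace the Yes/No column with the segment playing when the patient arrived, including credits or pause, plus an option for presence throughout the previous cycle.
2. **Appendix 2, part 3.** Define presence as presence for the full previous cycle. Keep the random and demographically diverse choice, and within it prefer later arrivals.
3. **Item 2f.** Split the count into patients present for the whole of the previous cycle and those present for part of it.
4. **Initial conditions.** Add a field for the playback option already established at check-in.
5. **Analysis plan, Section III.D.** For the select-patient half, report engagement by segment separately for first and repeat viewings on that visit. A viewing is a first viewing if the segment had not yet played since the patient arrived.

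The cost is one changed column, one split count, one added field and a few sentences, with no extra staff or visits. The real burden is on the single observer, who must note approximate arrival points for up to eight patients per assessment. At 6 to 8 assessments a day, that is at most 48 to 64 entries per site (8 × 6 and 8 × 8). Arrivals have to be noticed during the whole-room cycle, before the four are chosen, so some entries will be approximate. Exposure at earlier visits remains unknown. The change has to precede the one observation day at each site, because arrival points cannot be recovered afterwards.

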**IV. Summary comments**

After having watched the video for two cycles (once for the entire waiting room and once for the 4 patients), the observer will note any additional or summary comments with regard to engagement with the video, including whether engagement appeared to vary by demographics and by stories or segment of stories. The observer also will note whether there was a significant difference in the general conditions of the waiting room conditions for the two cycles that could have impacted patients’ engagement with the video.

**Appendix 3: Observation Instrument**

# Waiting Room Video Observation Data Collection Instrument

*[Simulated Survey Monkey display]*

## 1. Initial Waiting Room Conditions

### 1a.In which clinic are you observing today?

| Clinic |  | ⯆ |
| --- | --- | --- |
|  | Clinic 1 |  |
|  | Clinic 2 |  |
|  | Clinic 3 |  |
|  | Clinic 4 |  |

### 1b. What version of the video is playing?

| Video Version |  | ⯆ |
| --- | --- | --- |
|  | English only |  |
|  | English with Spanish subtitles |  |

### 1c. Is the video audible in most areas of the waiting room?

| 🞅 | Yes |
| --- | --- |
| 🞅 | No |

### 1d. How many monitors are playing?

| Number of monitors |  | ⯆ |
| --- | --- | --- |
|  | 0 |  |
|  | 1 |  |
|  | 2 |  |
|  | 3 |  |
|  | More than 3 |  |

### 1e. Use the space below to note any issues with the video or conditions in the waiting room that would likely impact patients’ experience watching the video.

|  | ▲ |
| --- | --- |
|  |  |
|  | ⯆ |

| **Next** |
| --- |

## 2. Observation of All Waiting Room Patients

### 2a. How many of the patients in the waiting room have an unobstructed view of the video?

|  |
| --- |

### 2b. How many of the patients can you see clearly enough to observe their reactions to the video?

|  |
| --- |

### 2c. Number of patients by apparent race/ethnicity in the waiting room

| American Indian/Alaska Native |  |
| --- | --- |
|  |  |
| Asian |  |
|  |  |
| Black/African American |  |
|  |  |
| Hispanic/Latino |  |
|  |  |
| Native Hawaiian/Other Pacific Islander |  |
|  |  |
| White |  |
|  |  |
| Other/Unsure |  |

### 2d. Number of patients by apparent age in the waiting room

| 25 or younger |  |
| --- | --- |
|  |  |
| 26 or older |  |
|  |  |
| Unsure |  |

### 2e. Number of patients by apparent gender in the waiting room

| Male |  |
| --- | --- |
|  |  |
| Female |  |
|  |  |
| Unsure |  |

### 2f. How many of these patients were present for any portion of the previous video cycle?

|  |
| --- |

### 2g. Opening: Enter general comments and any information relevant to patient engagement that you observed during this segment. For example, at what part of the opening did patients begin to take notice of the video? Did this seem to vary by race/ethnicity, age, or gender?

|  | ▲ |
| --- | --- |
|  |  |
|  | ⯆ |

### 2h. Story 1: Enter general comments and any information relevant to patient engagement that you observed during this segment. For example, did one part of the story seem to be particularly engaging or not engaging? Did this seem to vary by race/ethnicity, age, or gender?

|  | ▲ |
| --- | --- |
|  |  |
|  | ⯆ |

### 2i. Animation 1: Enter general comments and any information relevant to patient engagement that you observed during this segment. For example, did one part of the animation seem to be particularly engaging or not engaging? Did this seem to vary by race/ethnicity, age, or gender?

|  | ▲ |
| --- | --- |
|  |  |
|  | ⯆ |

### 2j. Story 2: Enter general comments and any information relevant to patient engagement that you observed during this segment. For example, did one part of the story seem to be particularly engaging or not engaging? Did this seem to vary by race/ethnicity, age, or gender?

|  | ▲ |
| --- | --- |
|  |  |
|  | ⯆ |

### 2k. Animation 2: Enter general comments and any information relevant to patient engagement that you observed during this segment. For example, did one part of the animation seem to be particularly engaging or not engaging? Did this seem to vary by race/ethnicity, age, or gender?

|  | ▲ |
| --- | --- |
|  |  |
|  | ⯆ |

### 2l. Story 3: Enter general comments and any information relevant to patient engagement that you observed during this segment. For example, did one part of the story seem to be particularly engaging or not engaging? Did this seem to vary by race/ethnicity, age, or gender?

|  | ▲ |
| --- | --- |
|  |  |
|  | ⯆ |

| **Prev** |  | **Next** |
| --- | --- | --- |

## 3. Observation of Select Waiting Room Patients

### 3a. Patient Apparent Demographics

Age Race/ethnicity Gender Present for previous cycle

| Patient 1 |  | ⯆ |  |  | ⯆ |  |  | ⯆ |  |  | ⯆ |  |
| --- | --- | --- | --- | --- | --- | --- | --- | --- | --- | --- | --- | --- |
| Patient 2 |  | ⯆ |  |  | ⯆ |  |  | ⯆ |  |  | ⯆ |  |
| Patient 3 |  | ⯆ |  |  | ⯆ |  |  | ⯆ |  |  | ⯆ |  |
| Patient 4 |  | ⯆ |  |  | ⯆ |  |  | ⯆ |  |  | ⯆ |  |
| Replacement 1 |  | ⯆ |  |  | ⯆ |  |  | ⯆ |  |  | ⯆ |  |
| Replacement 2 |  | ⯆ |  |  | ⯆ |  |  | ⯆ |  |  | ⯆ |  |
| Replacement 3 |  | ⯆ |  |  | ⯆ |  |  | ⯆ |  |  | ⯆ |  |
| Replacement 4 |  | ⯆ |  |  | ⯆ |  |  | ⯆ |  |  | ⯆ |  |
|  | 25 or younger |  |  | American Indian/Alaska Native |  |  | Female |  |  | Yes |  |  |
|  | 26 or older |  |  | Asian |  |  | Male |  |  | No |  |  |
|  | Unsure |  |  | Black/African American |  |  | Unsure |  |  |  |  |  |
|  |  |  |  | Hispanic/Latino |  |  |  |  |  |  |  |  |
|  |  |  |  | Native Hawaiian/Other Pacific Islander |  |  |  |  |  |  |  |  |
|  |  |  |  | White |  |  |  |  |  |  |  |  |
|  |  |  |  | Other/Unsure |  |  |  |  |  |  |  |  |

### 3b. Opening: Mark reactions or behaviors for each patient you are observing. Mark N/P if patient was not present for this segment. (Note all that apply)

|  | Began watching | Positive reaction | Negative reaction | Stopped watching | N/P |
| --- | --- | --- | --- | --- | --- |
| Patient 1 | □ | □ | □ | □ | □ |
| Patient 2 | □ | □ | □ | □ | □ |
| Patient 3 | □ | □ | □ | □ | □ |
| Patient 4 | □ | □ | □ | □ | □ |
| Replacement 1 | □ | □ | □ | □ | □ |
| Replacement 2 | □ | □ | □ | □ | □ |
| Replacement 3 | □ | □ | □ | □ | □ |
| Replacement 4 | □ | □ | □ | □ | □ |

### 3c. Opening: Note the duration of engagement (i.e. amount of the opening watched) for each patient during this video segment. Mark N/P if a patient was not present for this segment.

|  | All of it | More than half | Less than half | None of it | N/P |
| --- | --- | --- | --- | --- | --- |
| Patient 1 | 🞅 | 🞅 | 🞅 | 🞅 | 🞅 |
| Patient 2 | 🞅 | 🞅 | 🞅 | 🞅 | 🞅 |
| Patient 3 | 🞅 | 🞅 | 🞅 | 🞅 | 🞅 |
| Patient 4 | 🞅 | 🞅 | 🞅 | 🞅 | 🞅 |
| Replacement 1 | 🞅 | 🞅 | 🞅 | 🞅 | 🞅 |
| Replacement 2 | 🞅 | 🞅 | 🞅 | 🞅 | 🞅 |
| Replacement 3 | 🞅 | 🞅 | 🞅 | 🞅 | 🞅 |
| Replacement 4 | 🞅 | 🞅 | 🞅 | 🞅 | 🞅 |

### 3d. Enter information relevant to patient engagement that you observed during the Opening. For example, did one part of the opening seem to hold attention, lose attention, or elicit laughter or comment?

|  | ▲ |
| --- | --- |
|  |  |
|  | ⯆ |

### 3e. Story 1: Mark reactions or behaviors for each patient you are observing. Mark N/P if patient was not present for this segment. (Note all that apply)

|  | Began watching | Positive reaction | Negative reaction | Stopped watching | N/P |
| --- | --- | --- | --- | --- | --- |
| Patient 1 | □ | □ | □ | □ | □ |
| Patient 2 | □ | □ | □ | □ | □ |
| Patient 3 | □ | □ | □ | □ | □ |
| Patient 4 | □ | □ | □ | □ | □ |
| Replacement 1 | □ | □ | □ | □ | □ |
| Replacement 2 | □ | □ | □ | □ | □ |
| Replacement 3 | □ | □ | □ | □ | □ |
| Replacement 4 | □ | □ | □ | □ | □ |

### 3f. Story 1: Note the duration of engagement (i.e. watching video) for each patient during this video segment. Mark N/P if a patient was not present for this segment.

|  | All of it | More than half | Less than half | None of it | N/P |
| --- | --- | --- | --- | --- | --- |
| Patient 1 | 🞅 | 🞅 | 🞅 | 🞅 | 🞅 |
| Patient 2 | 🞅 | 🞅 | 🞅 | 🞅 | 🞅 |
| Patient 3 | 🞅 | 🞅 | 🞅 | 🞅 | 🞅 |
| Patient 4 | 🞅 | 🞅 | 🞅 | 🞅 | 🞅 |
| Replacement 1 | 🞅 | 🞅 | 🞅 | 🞅 | 🞅 |
| Replacement 2 | 🞅 | 🞅 | 🞅 | 🞅 | 🞅 |
| Replacement 3 | 🞅 | 🞅 | 🞅 | 🞅 | 🞅 |
| Replacement 4 | 🞅 | 🞅 | 🞅 | 🞅 | 🞅 |

### 3g. Enter information relevant to patient engagement that you observed during Story 1. For example, did one part of the story seem to hold attention, lose attention, or elicit laughter or comment?

|  | ▲ |
| --- | --- |
|  |  |
|  | ⯆ |

